### Phase 2: Pilot RCT

#### Overview

The overall aim of phase 2 is to assess the feasibility and acceptability of iMI4HIV and prepare the necessary research infrastructure and processes for a future fully powered RCT to test its efficacy in increasing MI skills among CSS in HIV-related interactions. Thus, we will recruit 30 CSS and randomize them using a 2:1 ratio (VMI workshop + iMI4HIV vs VMI workshop + waitlist control).

Figure 1 presents an overview of the phase 2 RCT procedures, detailing an RCT with a waitlist control arm which will gain access to iMI4HIV after completion of the Follow-Up 1 assessment. This design allows us to achieve the specific aims of the study as well as gain initial insights into the effects of iMI4HIV on MI skills and how these skills may be retained after 3 months. After all participants complete a baseline computer-assisted self-interview (CASI), they will complete SPI-1, then take part in the VMI workshop. After that, they complete SPI-2 and are then randomized into iMI4HIV versus a waitlist control. After 4 weeks, all participants complete Follow-Up 1, which consists of SPI-3, a follow-up CASI, and for only those in the iMI4HIV arm a qualitative interview. This will allow us to assess the feasibility and acceptability of iMI4HIV among those who were randomized into that arm (n=20). At this assessment point, we will also explore the effects of iMI4HIV on MI skills by comparing MI fidelity ratings of the SPI-3 between the intervention and control groups.

After Follow-Up 1, those in the control arm will be given access to iMI4HIV; after 4 weeks, only this group will complete Follow-Up 2, which will consist of SPI-4, a follow-up CASI, and an in-depth interview, which will provide additional acceptability data. Participants originally randomized into iMI4HIV will undergo their Follow-Up 2 after 12 weeks (SPI-4 and CASI, no QI). This will allow us to gain insights into retention of MI skills after 3 months, a key data point for a subsequent efficacy trial of iMI4HIV in which we would want to assess maintenance of MI skills. Community-based organizations rarely offer MI coaching to staff after a training workshop. Thus, we will not offer MI coaching in either study arm to focus on assessing the preliminary effects of iMI4HIV on participants’ MI skills.

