#### Randomization

As shown in Figure 1 above, after completing the SPI-2, participants will be randomized into iMI4HIV or waitlist control at a 2:1 ratio. After completing the VMI workshop, iMI4HIV participants will be sent a link to set up their account and access iMI4HIV. They will be asked to complete the online training within 4 weeks. Participants will receive weekly reminders to complete the training within 4 weeks, at which time access to the program will end. Waitlist control individuals will not have access to iMI4HIV during the 4 weeks following the VMI workshop but will get access once their follow-up assessment and SPI-3 are completed.

#### Follow-up Assessment 1

Four to 5 weeks after randomization, participants in both arms will complete the first follow-up assessment, which forms the basis for comparing the 2 RCT arms and will consist of a CASI and SPI #3. Participants in the iMI4HIV arm will also take part in a QI. Participants in the iMI4HIV arm who did not complete the program will still be invited to complete the follow-up assessment (for which there is an incentive) so we can learn about obstacles to completing the program and obtain their recommendations.

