##### Exploratory Outcomes

We will also explore the following outcomes:

MI skills acquisition. MITI-4.2 ratings for (1) Technical Component, (2) Relational Component, (3) Percent Complex Reflections, (4) Reflection:Question Ratio, (5) Total MI Adherent, and (6) Total MI Non-Adherent. Although the pilot RCT is not powered to detect differences between the intervention and control groups, we will compare these scores between the 2 groups for the SPI-3 assessment and within groups for each of the SPI assessments.Feasibility. Metadata from iMI4HIV, including mean (1) duration to complete specific iMI4HIV tasks, (2) number of times a lesson was completed prior to achieving a passing score, and (3) score for each task.Acceptability. Mean ratings on each of the generic TFA items (Affective Attitude, Burden, Intervention Cohesiveness, Self-efficacy, Ethicality, Perceived Effectiveness, and Opportunity Cost).

Data collected via assessments will be imported into IBM SPSS Statistics to calculate descriptive statistics for the sample. Estimation of the feasibility and acceptability outcomes (primary and exploratory) will be accomplished by generating the point estimate with its corresponding 95% CI. We will use a *t* test for continuous outcomes, and Fisher exact test for binary outcomes for the above comparisons. Adjustment for covariates, if necessary, with control baseline values, will be accomplished by multiple linear (continuous outcomes) or logistic (dichotomous outcomes) regression. While this study will not recruit a large enough sample to provide adequate power for assessing the efficacy of iMI4HIV, we will use data from MITI-4 ratings to explore specific changes in MI skills (listed in exploratory outcomes, above). To examine the efficacy of the addition of iMI4HIV on MI skills, the generalized linear model with identity and logit link function will estimate model parameters and their SEs for continuous and dichotomous variables, respectively. The generalized estimating equation method, with a robust SE estimator, will account for the within-subject correlation due to repeated measures from the same participant. Accompanying each of these tests will be point and interval estimates for the parameters of interest, such as group mean differences and odds ratios.

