##### Power Considerations

There is some controversy regarding the use of pilot data to estimate an actual effect size [111]; clinically meaningful effect sizes should be decided based on extrinsic, clinical judgment grounds, and not based on pilot data which are too few, typically, to obtain reliable conclusions. We can use pilot data to rule out unusually large or small true effects through standard 95% CI procedures. We will confirm that extrinsic effect sizes are contained within our CIs from the pilot. We will examine the distribution of each variable and calculate summary statistics by intervention condition. We will estimate key intervention parameters with sample means and proportions together with 2-sided 95% CIs and test the primary null hypotheses at the traditional 2-sided level α=.05 (to simulate the subsequent RCT). For planning the RCT, we will also consider 1-sided 90% confidence limits for mission-critical design parameters such as SDs and reference group end point rates and proportions in the conservative direction. This is because we intend to plan the sample size for the RCT so that power will be “excellent” (at least 80% power) for the clinically relevant effect size to be specified if our estimate of SDs is at the 1-sided 90% confidence limit in the conservative direction. This strategy will make proper allowance for the limited sample size of the pilot study with its consequent uncertainties, and still yield appropriate sample sizes for the future RCT. We will examine the strength of association between our primary outcome and key variables, with the view toward seeing if stratifying on such factors (eg, age and gender) would substantially reduce variability and increase the power of a future RCT. “Mission-critical” parameters include proportions for dichotomous end points; means and SDs for continuous end points; and response profiles for longitudinal studies. Large sample sizes are not required to locate these parameters approximately, but adequately, for planning the subsequent trial, whereas testing the study hypothesis in the pilot will generally not have sufficient statistical power. Estimation of mission-critical design parameters with point and CI estimates will be very important; continuous outcome measures make it feasible to detect promising effects even in small samples. For the continuous measures, means and SDs will be estimated. For approximately normally distributed variables, an upper 1-sided 90% confidence limit for the population SD, *s_U_*, will be constructed from *s_U_* = *s* × [(n – 1)/*x*^2^_0.10,_*_n_*_–1_]^1/2^, where *s* is the sample SD and *x*^2^_0.10,_*_n_*_–1_ is the upper 10th percentile of the chi-square distribution with *n* – 1 degrees of freedom. For approximately log-normally distributed variables, a logarithmic transformation will be applied to achieve approximate symmetry and normality. For the dichotomous variable, exact binomial methods will be used.

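### The efficacy GEE uses a robust SE on 20 vs 10 participants; read as the usual uncorrected form, its 95% intervals cover about 92.5%

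*Protocol article*

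**What the plan says.** The efficacy model is described in the protocol article, Quantitative Data Analysis, Exploratory Outcomes: "To examine the efficacy of the addition of iMI4HIV on MI skills, the generalized linear model with identity and logit link function" is to be used. The next sentence fixes the variance method: "The generalized estimating equation method, with a robust SE estimator, will account for the within-subject correlation due to repeated measures from the same participant". Point and interval estimates, such as group mean differences and odds ratios, are to accompany the tests. Neither a finite-sample correction nor a reference distribution is named.

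The sample is small and unequal. The Phase 2 Overview says "we will recruit 30 CSS and randomize them using a 2:1 ratio" and gives 20 for the iMI4HIV arm.

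On which visit compares the arms, the article is clearer. Exploratory Outcomes says "we will compare these scores between the 2 groups for the SPI-3 assessment and within groups for each of the SPI assessments". Follow-up Assessment 1 is described as the assessment "which forms the basis for comparing the 2 RCT arms". After Follow-Up 1, according to the Overview, "those in the control arm will be given access to iMI4HIV". The intervention arm's SPI-4 is there to look at skill retention.

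Power Considerations says that 95% CIs from the pilot can rule out unusually large or small true effects and will be checked for containing the extrinsic effect sizes.

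**The concern.** The sandwich variance is justified by a large number of independent participants. With few, the fitted residuals are smaller than the true errors, so the variance is estimated too low. The z reference also ignores the uncertainty in that estimate. Both faults make intervals too short and P values too small, and the smaller arm of 10 contributes most of the problem.

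The pilot tells readers not to rely on its significance tests, but it does rely on its intervals. An interval that is too short can exclude an effect size that the data do not rule out, which is the use Power Considerations has in mind. The same section stresses allowance for the small sample and builds a conservative limit for the SD. An efficacy model without such an allowance is out of step with that aim.

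**Working it through.** **Inputs from the article.** 30 participants randomized 2:1, so 30 × 2/3 = 20 and 30 × 1/3 = 10; this reproduces the stated 20. Two-sided α = .05 and 95% CIs. GEE, identity link for continuous outcomes, robust SE.

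**Assumptions not in the article.** Normal outcomes; complete data at the stated arm sizes; within-person correlation 0.3, 0.5 or 0.7; in the repeated-measures runs, a true SPI-3 effect of 0.6 SD and an exchangeable working correlation set at its true value. For SPI-4: full retention in the intervention arm, and controls reaching the full effect.

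**Step 1: bias of the variance (exact, single-visit contrast).** With n₁ and n₀ per arm and common variance σ²:
- true variance = σ²(1/n₁ + 1/n₀)
- expected uncorrected sandwich variance = σ²[(n₁ − 1)/n₁² + (n₀ − 1)/n₀²]
- 20 vs 10: (19/400 + 9/100)/(1/20 + 1/10) = 0.1375/0.1500 = 91.7%
- 16 vs 8: (15/256 + 7/64)/(1/16 + 1/8) = 0.1680/0.1875 = 89.6%

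**Step 2: rough effect on width.** The SE is low by a factor of about √0.917 = 0.957. Using z instead of t with 28 df gives 1.960/2.048 = 0.957. Together 0.957 × 0.957 = 0.916, so the interval is about 8% short before sampling variation of the SE is counted.

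**Step 3: coverage by simulation (single visit, 200,000 replicates).**

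| Method | Coverage, 20 vs 10 | Mean half-width (SD), 20 vs 10 | Coverage, 16 vs 8 |
|---|---|---|---|
| Uncorrected robust, z | 92.5% | 0.717 | 91.8% |
| Kauermann-Carroll, t | 94.6% | 0.783 | 94.5% |
| Mancl-DeRouen, t | 95.5% | 0.818 | 95.6% |
| Pooled t | 95.0% | 0.786 | 95.1% |
| Welch t | 95.0% | 0.804 | 95.1% |

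Two-sided error for the uncorrected form is 100 − 92.5 = 7.5% at 20 vs 10, and about 8.3% at 16 vs 8 (unrounded coverage 91.75%). Width: 0.717/0.786 = 0.912, about 9% narrower than pooled t; 0.717/0.804 = 0.892, about 11% narrower than Welch. At 100 vs 50 the uncorrected form covers 94.5%, so the fault comes from the sample size.

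**Step 4: repeated-measures GEE (20 vs 10, 4,000 replicates per setting).** For models that estimate the SPI-3 contrast, uncorrected coverage is 91.4% to 92.8%. Mancl-DeRouen with t on 28 df gives 94.6% to 96.2%.

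**Step 5: does SPI-4 matter?** With visit-specific group terms, keeping SPI-4 in the model leaves the SPI-3 estimate at 0.59 to 0.61 against a true 0.60. One common post-randomization effect over SPI-3 and SPI-4 gives 0.30, half the true value, with uncorrected coverage of 64% to 77%. The article states no such model.

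**The case against.** **The word uncorrected is inferred.** Corrected sandwich estimators are also robust estimators, and the choice of correction and degrees of freedom could sit in an analysis plan that is not shown. This stands as a caveat. But the article goes as far as naming the model, links, estimation method and SE type, and a robust SE named without qualification is ordinarily the plain sandwich.

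**Little depends on it.** The outcomes are exploratory and the article says the arm comparison is not powered. The SPI-3 comparison also has a t test or Fisher exact test, neither of which uses the sandwich. Progression rests on 70% completion and 80% acceptability, and the future sample size on an extrinsic effect size and an upper limit for the SD. All of this stands and keeps the point small. A reader might infer that the plan's 5% tests in general are wrong, since Power Considerations will "test the primary null hypotheses at the traditional 2-sided level" of .05. The article does not support that: its primary outcomes are the completion and acceptability percentages, which this model does not estimate.

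**SPI-4.** A reader might also infer that the GEE pools all four SPIs, so that crossover contaminates the effect; one constant arm effect over four visits would recover only (0 + 0 + 1 + 0)/4 = 25% of the SPI-3 effect. The article does not support this either. It places the between-arm comparison at SPI-3, before controls gain access, and assigns the other SPIs to within-group comparison. A constant-effect model is nowhere stated. It is also a different model from the visit-specific one behind the 7.5%, so the two figures cannot describe the same analysis.

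**Conclusion.** The variance point holds, in modest form. If the robust SE is the usual uncorrected one with a z reference, 95% intervals for the efficacy contrast cover about 92.5% at 20 vs 10, and two-sided error rises by about 2.5 percentage points, or about 3.3 at 16 vs 8. This rests on normal outcomes and the identity link. The logit link was not simulated, but the six MI skill outcomes listed are scores, percentages, ratios or totals, so the identity link is the relevant case. The design and the primary outcomes are unaffected.

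SPI-4 contamination does not follow from the plan as written. What remains is that the GEE sentences do not themselves name the contrast that the rest of the article names.

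**What to change.** State that the GEE will use a small-sample-corrected robust SE (Kauermann-Carroll or Mancl-DeRouen) with a t reference. For continuous outcomes, a linear mixed model with Kenward-Roger or Satterthwaite degrees of freedom is an alternative. If an existing analysis plan already says this, a cross-reference is enough.

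As a clarification, add one sentence: the model's between-arm contrast is the SPI-3 difference, with SPI-4 either left out or given its own group-by-visit term, because controls have had iMI4HIV by then. The arms' SPI-4 also falls at different times since access: about 4 weeks for controls and about 4 + 12 = 16 weeks for the intervention arm.

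The cost is a sentence or two and slightly wider intervals: at 20 vs 10, from 0.717 SD to between 0.783 and 0.818 SD in half-width. The article names IBM SPSS Statistics, so check that the chosen option is available there. Recruitment, visits and data collection do not change.

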##### Power Considerations

There is some controversy regarding the use of pilot data to estimate an actual effect size [111]; clinically meaningful effect sizes should be decided based on extrinsic, clinical judgment grounds, and not based on pilot data which are too few, typically, to obtain reliable conclusions. We can use pilot data to rule out unusually large or small true effects through standard 95% CI procedures. We will confirm that extrinsic effect sizes are contained within our CIs from the pilot. We will examine the distribution of each variable and calculate summary statistics by intervention condition. We will estimate key intervention parameters with sample means and proportions together with 2-sided 95% CIs and test the primary null hypotheses at the traditional 2-sided level α=.05 (to simulate the subsequent RCT). For planning the RCT, we will also consider 1-sided 90% confidence limits for mission-critical design parameters such as SDs and reference group end point rates and proportions in the conservative direction. This is because we intend to plan the sample size for the RCT so that power will be “excellent” (at least 80% power) for the clinically relevant effect size to be specified if our estimate of SDs is at the 1-sided 90% confidence limit in the conservative direction. This strategy will make proper allowance for the limited sample size of the pilot study with its consequent uncertainties, and still yield appropriate sample sizes for the future RCT. We will examine the strength of association between our primary outcome and key variables, with the view toward seeing if stratifying on such factors (eg, age and gender) would substantially reduce variability and increase the power of a future RCT. “Mission-critical” parameters include proportions for dichotomous end points; means and SDs for continuous end points; and response profiles for longitudinal studies. Large sample sizes are not required to locate these parameters approximately, but adequately, for planning the subsequent trial, whereas testing the study hypothesis in the pilot will generally not have sufficient statistical power. Estimation of mission-critical design parameters with point and CI estimates will be very important; continuous outcome measures make it feasible to detect promising effects even in small samples. For the continuous measures, means and SDs will be estimated. For approximately normally distributed variables, an upper 1-sided 90% confidence limit for the population SD, *s_U_*, will be constructed from *s_U_* = *s* × [(n – 1)/*x*^2^_0.10,_*_n_*_–1_]^1/2^, where *s* is the sample SD and *x*^2^_0.10,_*_n_*_–1_ is the upper 10th percentile of the chi-square distribution with *n* – 1 degrees of freedom. For approximately log-normally distributed variables, a logarithmic transformation will be applied to achieve approximate symmetry and normality. For the dichotomous variable, exact binomial methods will be used.

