### Study Objectives

The overall goal of the study is to develop and pilot an interactive, gamified, online training program in MI for HIV CSS to improve health communication in status-neutral HIV care interactions. This National Institutes of Health (NIH) R34 (Clinical Trial Planning Grant) study will allow us to pilot all the components and build the necessary research infrastructure for a subsequent randomized controlled trial (RCT) that is fully powered to assess the efficacy of iMI4HIV in increasing MI skills among CSS in HIV care interactions. The specific aims of this R34 study are as follows:

Develop iMI4HIV, an interactive, online, gamified MI training program specifically tailored toward CSS in HIV care settings to improve their MI skills with HIV care clients.Conduct a pilot RCT of a virtual motivational interviewing (VMI) workshop + iMI4HIV versus VMI workshop + waitlist control (n=30) to (1) assess the feasibility and acceptability of iMI4HIV as measured by participant completion rate and retrospective acceptability ratings of iMI4HIV, and (2) explore preliminary findings on the effects of iMI4HIV on MI skills acquisition using Standard Patient Interactions (SPIs).Explore experiences (including engagement, obstacles, and facilitators) of completing iMI4HIV via in-depth interviews with pilot study participants.

In this paper, we present the proposed procedures for developing iMI4HIV, conducting the pilot RCT, and assessing its acceptability among HIV CSS.

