#### Baseline Assessments

After enrolling, participants will receive an email with a link to the CASI to be completed within 7 days and will be scheduled for their SPI-Baseline session, which will be audio-recorded and rated for MI fidelity. The CASI and the SPI-Baseline must be completed prior to the MI workshop. The baseline CASI assessment will include the following:

Demographics. This will capture information on age, gender, race, ethnicity, education, primary language, counseling training, and prior MI training.MI Knowledge and Attitudes Test (MIKAT) [101], a 29-item assessment that has shown sensitivity to detect change in MI consistent and inconsistent behavior in pre- and posttraining comparisons [101-104], with acceptable internal consistency [104]. The MIKAT will be adapted to diminish its focus on MI for substance use treatment.Perceptions of Evidence-Based Practices (EBPs) will be evaluated using 4 self-report measures:The Evidence-Based Practice Attitudes Scale-15 [105] is a 15-item assessment of providers’ attitudes toward EBPs, with 4 factors: Appeal, Requirements, Openness, and Divergence. Participants will also complete 2 assessments of their perceptions of how EBPs are viewed by their supervisor and at the agency.The Implementation Climate Scale [106], reliably assesses the extent to which a clinic fosters EBP implementation.The Implementation Leadership Scale [107] assesses leadership support for EBP implementation.TFA quantitative questionnaire [100]. Finally, we will assess the prospective acceptability of iMI4HIV using a tailored version of the generic TFA questionnaire. This questionnaire is composed of a 5-point Likert-type scale for each of the TFA components and 1 general question on acceptability. Findings from phase 1 will also identify other areas of inquiry for the baseline CASI.SPIs. We will use scheduling software for study participants to schedule their SPIs. At the specified time, the SPI actor will contact the participant by phone to conduct a 15-minute MI session focused on an HIV care scenario. The session will be audio-recorded and then rated using the Motivational Interviewing Treatment Integrity ratings (MITI 4.2) [108], a valid and reliable measure of MI skills [109]. MI skills will be assessed at baseline, postworkshop, post iMI4HIV, and 3 months later (for participants randomized into iMI4HIV).

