#### Quantitative Data Analysis

##### Primary Outcomes

The primary outcomes of the pilot study will be based on the phase 2 RCT pilot, including (1) the percent of study participants that complete iMI4HIV within 4 weeks posttraining workshop (feasibility) and (2) the percentage of participants that respond Acceptable or Completely Acceptable to the question, “How acceptable was iMI4HIV to you?” from the TFA generic acceptability questionnaire (acceptability).

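### Stratification factors for the future RCT are to be sought by association with the pilot's primary outcome, defined as completion and acceptability, although that RCT will test MI skill

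*Protocol article*

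**What the plan says.** Four parts of the protocol article bear on this.

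- **Power Considerations** sets the analysis: "We will examine the strength of association between our primary outcome and key variables". Its purpose is to learn whether stratifying on such factors, with age and gender as examples, "would substantially reduce variability and increase the power of a future RCT".
- **Primary Outcomes** fixes the term. "The primary outcomes of the pilot study will be based on the phase 2 RCT pilot", and two are listed: "the percent of study participants that complete iMI4HIV within 4 weeks posttraining workshop (feasibility") and "the percentage of participants that respond Acceptable or Completely Acceptable to the question" on overall acceptability in the TFA questionnaire. No other primary outcome is defined.
- **Exploratory Outcomes** is where MI skill appears: "MI skills acquisition. MITI-4.2 ratings for (1) Technical Component, (2) Relational Component, (3) Percent Complex Reflections", followed by three further ratings. None of the six is marked as the intended endpoint of the later trial.
- **Study Objectives** says that the later trial will be "fully powered to assess the efficacy of iMI4HIV in increasing MI skills among CSS in HIV care interactions". The Phase 2 Overview says the same in substance.

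**The concern.** A stratification or adjustment factor raises a trial's power only to the extent that it explains variance in that trial's own endpoint. Here the endpoint will be MI skill, while the outcome named for choosing factors is completion or acceptability of the training program. These are different quantities. They are measured on different scales, and at the time of the between-arm comparison they are measured in different sets of participants.

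An analyst who follows the two sections as written would rank factors by how well they predict finishing the program or liking it. That could put forward factors with no value for the RCT's power and pass over factors that matter for skill. The study is funded by a planning grant whose purpose is to inform that RCT, so the error would fall on one of its intended products.

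**Working it through.** The plan gives no variance reduction, correlation or sample size calculation for this step, so there is no figure of its own to reproduce. The check is mainly a comparison of sections; the arithmetic is illustrative.

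**1. Which outcome, in whom**

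| | Outcome named for the analysis | Endpoint the analysis is meant to serve |
|---|---|---|
| Definition | Completion; acceptability (Primary Outcomes) | MI skill (Study Objectives; Phase 2 Overview) |
| Scale | Binary | MITI-4.2 ratings |
| Available at Follow-Up 1 | iMI4HIV arm only, n=20 | Both arms through SPI-3, up to 30 |

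Waitlist participants supply completion and acceptability data later, at Follow-Up 2, after they too have been given the program. There is then no between-arm contrast on these outcomes.

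**2. Does association with completion stand in for association with skill?** Let b be a factor's correlation with completion and ρ the correlation between completion and skill. The factor's correlation with skill can lie anywhere in

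bρ ± √[(1 − b²)(1 − ρ²)].

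Both b and ρ are assumed; the documents give neither.

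- b = 0, ρ = 0.5: 0 ± √(1 × 0.75), that is -0.87 to 0.87.
- b = 0.3, ρ = 0.3: 0.09 ± √(0.91 × 0.91) = 0.09 ± 0.91, that is -0.82 to 1.00.

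So neither a null nor a moderate association with completion settles whether the factor explains skill.

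**3. What the literal analysis could detect.** Take 14 of 20 completers, which is the article's 70% feasibility benchmark, and a binary factor split 10/10 (assumed). By Fisher's exact test, 10/10 against 4/10 gives p=0.011, while 9/10 against 5/10 gives p=0.14. Only the most extreme split reaches 0.05.

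**4. Why the right correlation matters.** With linear adjustment for a factor correlated r with the endpoint, the residual variance is multiplied by 1 − r², and the required sample size falls in about the same proportion. For a standardised difference of 0.5, two-sided α of 0.05, 80% power and 1:1 allocation (the difference and allocation are assumptions):

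| r (assumed) | 1 − r² | Total N |
|---|---|---|
| 0 | 1.00 | 126 |
| 0.3 | 0.91 | 116 |
| 0.5 | 0.75 | 96 |
| 0.7 | 0.51 | 66 |

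This r is the quantity that the analysis, read literally, does not estimate.

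**5. Precision if the outcome is corrected.** The Fisher z interval is tanh[atanh(r) ± 1.96/√(n − 3)].

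- r = 0.5, n = 30: 0.17 to 0.73.
- r = 0.5, n = 28 (two participants assumed lost): atanh(0.5) = 0.549 and 1.96/√25 = 0.392, giving 0.16 to 0.74. Squared, this is a variance reduction of about 3% to 55%.
- r = 0, n = 20: ±0.44. At n = 30: ±0.36.

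The correction directs the estimate at the right quantity and uses more participants. It does not make the estimate precise.

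**The case against.** The strongest reply is that the authors meant MI skill. The sentence uses the singular although two primary outcomes are defined, it stands among text on planning the later RCT, and its stated aim makes sense only for an efficacy endpoint. This reading is plausible. But no section redefines the term, and under this reading it contradicts the Primary Outcomes section and still does not say which of six MITI ratings is meant. The text needs correcting either way.

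A second reply is that Exploratory Outcomes already allows regression adjustment and repeated-measures models of the MITI ratings. It does, but the covariate adjustment is conditional on need and is not linked to choosing strata.

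Some stronger readings are tempting, and the documents do not support them:

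- **That the pilot cannot show which factors explain MI skill.** The limitation lies in the wording, not the data. MITI ratings are collected in both arms, and the right association could be calculated from them.
- **That leaving out SPI-2 score and prior MI training is an error.** Age and gender are given only as examples, so the list is open and excludes nothing.
- **That the waitlist arm is untrained.** Both arms complete the VMI workshop before randomization. Controls lack only iMI4HIV up to Follow-Up 1.
- **That a definite sample size saving is being lost.** Every r above is assumed, and the pilot would estimate it only roughly.

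**Conclusion.** The point holds as a mismatch between a named outcome and the stated purpose of its analysis. On the article's own definitions, the search for stratification factors uses completion or acceptability, while the trial it is meant to help will test MI skill. If skill was intended, the term is used against its definition.

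The consequence is limited. The pilot's primary estimates, its between-arm comparisons and its progression thresholds (70% completion, 80% acceptability) are not affected. What is affected is one planning output for the RCT. Its possible value can be illustrated (a 25% smaller variance at an assumed r of 0.5) but cannot be established from the documents. The conclusion itself rests on the article's definitions and on no assumed figure.

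**What to change.** In Power Considerations, replace the reference to the primary outcome with the MITI-4.2 score intended as the future RCT's endpoint, measured at SPI-3. Use both arms (up to 30 participants), allow for arm, and report the partial correlation or R-squared with its 95% CI. This means saying which of the six ratings is intended. The interval should be read as a guide to planning only, given its expected width.

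As an optional improvement and not a correction, two variables could be named among the candidates beside age and gender: the SPI-2 score, which precedes randomization, and prior MI training, which the baseline questionnaire already records ("primary language, counseling training, and prior MI training"). Predictors of completion and acceptability can be kept as a separate feasibility question.

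The cost is about one sentence of analysis text. No new data, visits or participants are needed.
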